| INTERVIEW AND DATA COLLECTION  Interviews will be conducted in 2 stages:   1. Intake interview: in one 30-minute survey presented over the internet (or in person, or by paper and pencil), we will present subjects with a one-page summary sheet describing each replication study (see Appendix 2), as well as a questionnaire (see Appendix 3). Individuals will be approached using appropriate elicitation technique, whereby we first a) describe the goals of the project and how to complete the questionnaire; b) attempt to motivate good performance by explaining how scoring works; c) provide a simple warm up question (asking for a weather forecast); d) elicit replication forecasts; and e) collect additional cognitive and attitudinal measures. The questionnaire will first collect forecasts, then individual difference variables (as applicable), then demographic variables. 2. Forecasts: subjective probabilities on target experiments.    - 1. 2 binary: Significant difference and direction on 3 replication studies      2. 2 @ 4 parameter simplified continuous (best estimate, range, confidence) on overall replication rates.    1. Individual difference variables       1. Actively Open-Minded Thinking[10]       2. Pace of progress of medical research (AKA Medical Boomster-Doomster, adapted from [11])       3. Self-report of expertise for each study       4. Confidence rating of each forecast       5. Time for forecasts       6. Evidence reliance       7. Familiarity with and Anticipated Impact of Reproducibility Project       8. Estimate of perfect replication of effect sizes    2. Demographics:       1. age       2. gender       3. expertise: H index, title/rank (associate professor, full professor, etc.), number of publications, number of citations (all collected from both SCOPUS & Web of Science), nationality/region 3. Post-event Interview: Once results are available, all participants will be approached for posterior and recalled forecasts. We will collect the first set of posterior distributions when the first batch of results is published. Once all data are collected, we participants will be debriefed about study hypotheses and offered an opportunity to learn their forecast skill against the average of their peers. |

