| PRIMARY ANALYSIS  We will calculate the Brier scores of each individual forecaster, and present a distribution. A Brier score is a proper scoring rule – meaning it incentivizes honest reporting of subjective beliefs – which measures the accuracy of a forecast: BS = 1/N $\sum_{i=1}^{N} \left( f_{i}-o_{i} \right)^{2}$ where *f_i_* is a forecast and *o_i_* is a realized outcome for each of i events.[12] We will decompose into calibration = 1/N $\sum_{i=1}^{N} {1/n_{i}\left( f_{i}-\bar{o}_{i} \right)}^{2}$, and discrimination = 1/N $\sum_{i=1}^{N} 1/n_{i}(\bar{o}_{i}\left( 1-\bar{o}_{i} \right))$.[13] We will construct calibration curves for individual forecasters. Our null hypothesis is that mean Brier score 95% confidence intervals exclude Brier score for a matched sample size of hypothetical forecasters predicting same trials using a random number generator. We will also measure the Brier Skill Score for individuals: BSS = 1 – BS/BS_ref_ where BS_ref_ is the base rate for the reference class or of a confidence interval. The sample variance can be used when is BS_ref_ unknown.[14]  Primary endpoint   1. Replicability rate measures: The brier scores for aggregate measures will be slightly higher than .25 (note: .25 is the equivalent of a 50-50 prediction meaning “I don’t know” or a random guess). The mean forecaster will perform slightly worse than base-rates. Forecasts will be skewed toward predicting more successful replications than observed, but less than statistically expected. The order of successful predictions of aggregate replicability rates will be: 2. Effect sizes at least as large (Brier of about .20 to .25) 3. Significance (p-values) (Brier of about .25)   An a priori power analysis suggests we need a sample size of 34 to detect if expert Brier scores are different than a constant (e.g. random guessing (BS = .25) or a base rate (e.g. 80% of significant effects in cancer phase 3 trials favor the new treatment[15]) by a moderate degree (difference from a constant of Cohen’s d = .5) assuming power = .80 and alpha = .05.   1. Individual study measures: The Brier scores for individual studies will be slightly lower than .25. Forecasts will predict more successful replications than observed. Brier scores will be lower (forecasts will be more successful) for forecasting the direction of the difference between effect sizes (Outcome2) compared to forecasting significant differences (Outcome1). Base-rates will outperform the typical forecaster, but aggregating the top-tier of forecasters will beat base-rates. |

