| SECONDARY ANALYSIS ON FORECAST SKILL^[[4]](#footnote-4)^  An a priori power analysis suggests we need a sample size of 34 per group to detect if detect if the experts differ from (d = .5) the novice group assuming power = .80 and alpha = .05, and we need about 180 total respondents to detect a moderate difference (f = .25) between all four strata. As analysis is exploratory, we do not intend to correct for multiple hypothesis testing.   1. Expert strata analysis: 2. The order of predicted replication rates will be: 3. Novices/Non-experts (Should be optimistic since and less attuned to the “replicability crisis” across scientific disciplines) 4. Originators (if available- should be optimistic due to their investment in these results, but more realistic than novices) 5. Independent Experts (Should be less biased due to independence from findings) 6. Replicators (if available- theoretically well attuned to flawed research design and practices) 7. The order of forecast skill will be: 8. Independent Experts (should have sufficient expertise and less biased by own work) 9. Originators (if available- should have sufficient expertise, but more myside bias) 10. Replicators (if available- assumes lab skills are higher than knowledge for this group) 11. Novices/Non-experts (assuming expertise and forecast skill are related, they have the least expertise) 12. The order of variability in forecasts will be: 13. Novices/Non-experts (assuming expertise and forecast skill are related, there should be more variability for those with the least knowledge) 14. Independent Experts 15. Replicators (if available- assumes replicators are well attuned to good and bad study design and difficulty of carrying out certain studies) 16. Originators (if available- assuming expertise and forecast skill are related, there should be less variability in recognizing real empirical relationships and flawed study design by those who have devoted their lives to studying these topics) 17. Expertise will have an inverse U-shaped (∩) relationship with forecasting success. People with low expertise will perform poorly due to inadequate information, and people with high expertise will perform poorly due to maladaptive beliefs (e.g. confirmation bias). The correlation between perceived expertise and Brier score will be ranked as follows:      1. Originators (if available- should perform when they claim higher expertise; have motivation to honestly claim high expertise for some, but not all topics) 2. Independent Experts (may be less discriminating in expertise ratings than originators since they don’t have personal relationships with any of the studies) 3. Replicators (if available) 4. Novices/Non-experts (should have consistently low expertise ratings) 5. Predictors of Forecast Skill: We will test the relationship between each demographic and scale variables and Brier Skill Score, secondarily looking at components of calibration and discrimination. The individual differences should influence the forecasts in the following order (from most to least influential). 6. More extreme updaters: Those who update more extremely relative their will have more accurate forecasts^[[5]](#footnote-5)^. 7. Pace of progress: Those who believe medical technology should progress quickly (slowly) will have more optimistic (pessimistic) forecasts. 8. Evidence reliance: 9. Those who rate the methodology of the replication attempt as important will be pessimistic. 10. Those who cite specific trial outcomes as evidence will be worse forecasters, and those who cite treatment or disease type (base rates) will be better forecasters. 11. Expertise: Those will high (self-reported and actual) expertise will be more accurate; actual expertise (H- & M-indices) will be more predictive of forecasting skill. 12. Confidence will be weakly correlated with forecasting skill. We expect a hard-easy effect where forecasters are overconfident on hard items and underconfident on easy items. 13. Demographics     1. We will also test methods of identifying forecasting skill early (prior to target event realization) the relationship between individual forecaster’s Brier scores and their average squared distance to the median compared to other baselines (mean, expectation due to chance, expectation due to base rates if available) - we hypothesize that this will lead to a strong relationship with forecast skill. 14. Aggregation of Forecasts 1: We will test whether different aggregation approaches give better forecast performance (i.e. lower Brier scores). First, to determine the relative value of using combined forecasts to make decisions, we will construct a curve of showing the relationship between Brier scores and number of aggregated forecasts. Specifically, the curve will reflect n=0 aggregation (i.e. average Brier scores of individual forecasters); n=1 (i.e. average Brier score when two forecasters forecasts are randomly aggregated); n=4 (i.e. average Brier score when 5 randomly selected forecasts are aggregated); and n=9 (i.e. average Brier score when 10 randomly selected forecasts are aggregated). We will also use transformations to make predictions more extreme.[16,17] 15. Predictors and Aggregation: Using individual differences and demographic variables that show low skill identified in step 1, we will test the competitiveness of aggregated low skill forecasters with the individual scores of high skill forecasters. For instance, suppose we find a relationship between high M-index and high forecast skill. We will then test whether, if we combine forecasts from 2, 3, 5 and 10 low M-index forecasters, on average the forecast outperforms the average forecast of high M-index forecasters.   After we have completed forecast scoring, we will also rank all individual forecasters by their Brier skill scores, and randomly select individuals within tiers of upper, middle, and lower thirds. We will test whether combined forecasts of 2, 3, 5 and 10 “low skill” forecasters can, on average, beat the forecast of randomly selected individuals from each skill tier. Brier scores will be used; as well, they will be decomposed into discrimination and calibration. |

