**Protocol Appendix**

**Survey Versions**

1. Expert survey 1
   1. Studies 15, 21, & 44
2. Expert survey 2
   1. Studies, 19, 29, & 39
3. Expert survey 1, incentive pilot:
   1. Studies 15, 21, & 44
   2. included option to list email for us to send C$20 Amazon gift card or donate $20 to Canadian Cancer Society
4. Expert survey 2, incentive pilot:
   1. Studies, 19, 29, & 39
   2. included option to list email for us to send C$20 Amazon gift card or donate $20 to Canadian Cancer Society
5. Novice survey 1
   1. Studies 15, 21, & 44
   2. Exclude: Editor question
   3. Include:
      1. Cancer class or lab semesters question
      2. Add email to obtain results

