3. We did not pursue these additional strata because we anticipated great difficulty accessing a sufficient sample of originators, after being advised about the controversial nature of the project and the fact that many felt over-extended due to time spent gathering and recreating original materials. Ultimately, without the originator stratum and due to their access to results, we decided not to pursue the replicators stratum either. [↑](#footnote-ref-3)
4. Analyses might not all be included in a single manuscript. We are not able to conduct some of the analyses described due to the lack of variability in observed replication results and since we excluded a couple of secondary expert strata. [↑](#footnote-ref-4)
5. We cannot measure belief updating until all of the replication results are announced and we collect posterior forecasts. [↑](#footnote-ref-5)

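### The sample-variance fallback for the individual Brier skill score can be zero, and otherwise sets the no-skill point from the few outcomes being scored

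*Protocol*

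**What the plan says.** PRIMARY ANALYSIS defines the skill score and its reference: "We will also measure the Brier Skill Score for individuals: BSS = 1 – BS/BS_ref_ where BS_ref_ is the base rate for the reference class". It then gives a fallback: "The sample variance can be used when is BS_ref_ unknown". It does not say which sample is meant, which divisor applies, or what happens when the reference is zero.

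The number of outcomes per person is small. INTERVIEW AND DATA COLLECTION lists "2 binary: Significant difference and direction on 3 replication studies", and the Survey Versions appendix gives one set as "Studies 15, 21, & 44" and the other as "Studies, 19, 29, & 39". SAMPLING also has a sentence in which participants forecast all six studies, but the same section then splits the studies into two surveys.

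No replication base rate is fixed. The only numerical one, 80%, is an example taken from phase 3 trials. SECONDARY ANALYSIS ON FORECAST SKILL treats base rates as conditional: "expectation due to base rates if available".

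Footnote 4, attached to that secondary section, says: "We are not able to conduct some of the analyses described due to the lack of variability in observed replication results".

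**The concern.** A skill score needs a reference that is never zero and that means the same thing for everyone compared on it. The variance of three to six binary outcomes guarantees neither. If the outcomes agree, the score divides by zero. If they do not, the reference is computed from the very results being forecast, so zero no longer marks a forecaster without skill.

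The skill score is used in three places: the coded website showing each participant's position on one distribution (INCENTIVIZING GOOD PERFORMANCE), the ranking of all forecasters into thirds, and the tests of demographic and scale predictors (both SECONDARY ANALYSIS ON FORECAST SKILL). Nothing there separates the two survey versions, although each has its own studies and hence its own outcomes.

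**Working it through.** **Inputs.** BSS = 1 − BS/BS_ref and the variance fallback (PRIMARY ANALYSIS); three studies and two binary questions per survey (INTERVIEW AND DATA COLLECTION; Survey Versions). The protocol gives no replication rate, so the success rate p is an assumption, shown over a range.

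**The plan's own figure.** It puts the Brier score of a 50-50 answer at .25. This is reproduced: (.5 − 0)² = (.5 − 1)² = .25. It gives no figure for BS_ref under the fallback.

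**Step 1: chance that the reference is zero.** For n independent outcomes at rate p, the probability that all agree is pⁿ + (1 − p)ⁿ.

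| p | n = 3 | n = 6 |
|---|---|---|
| .5 | .125 + .125 = .25 | .0156 + .0156 = .03 |
| .3 | .027 + .343 = .37 | .0007 + .1176 = .12 |
| .2 | .008 + .512 = .52 | .0001 + .2621 = .26 |

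The values are the same at .7 and .8 by symmetry. For one question with n = 3, the chance that at least one of the two surveys has a zero reference is 1 − (1 − q)², where q is the n = 3 entry: .44, .60 and .77.

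**Step 2: value of the reference when it exists, n = 3.** With one or two successes, ō(1 − ō) = (1/3)(2/3) = .222 with divisor N, and .222 × 3/2 = .333 with divisor N−1. A 50% answer has BS = .25, so
- divisor N: 1 − .25/.222 = −.125
- divisor N−1: 1 − .25/.333 = +.25

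The unstated divisor decides whether an uninformed answer shows negative or positive skill.

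**Step 3: why divisor N is a hindsight benchmark.** For a constant forecast c, the mean of (c − o)² equals ō(1 − ō) + (c − ō)². The variance is therefore the score of someone who stated the observed rate, and no constant forecast can beat it.

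**Step 4: a forecaster who states the true rate, n = 3.** At p = .5 the forecast is 50%, so the score, where defined, is −.125 or +.25 as in Step 2. At p = .8, one success has probability 3 × .8 × .04 = .096 with BS .44, and two successes have probability 3 × .64 × .2 = .384 with BS .24. Given that the score is defined, its mean is
- divisor N: [.096 × (−.98) + .384 × (−.08)]/.48 = −.26
- divisor N−1: [.096 × (−.32) + .384 × .28]/.48 = +.16

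**Step 5: comparing the two surveys.** Per question with n = 3, every defined reference is the same (.222 or .333), so the surveys can differ only as defined versus undefined. If both questions are pooled (n = 6, divisor N), references can also be unequal. One success in six gives (1/6)(5/6) = .139 and three give .25. A Brier score of .20 then becomes 1 − .20/.139 = −.44 in one survey and 1 − .20/.25 = +.20 in the other.

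**The case against.** The fallback is permissive and conditional, and the stated reference is a base rate. The sample is not named. It could be six outcomes rather than three, which cuts the zero-variance risk roughly to the n = 6 column. It could also be all six studies on one question, in which case both surveys share a reference and the cross-survey problem disappears. Sample, divisor and a zero rule might be set in a statistical analysis plan, which is not at hand. Within one survey and question, a non-zero reference is common to everyone, so ranking by skill score equals ranking by Brier score. Outcome dependence across surveys is not peculiar to the fallback either: an 80% base-rate forecast has a realised Brier score of .64, .44, .24 or .04 for 0 to 3 successes in three.

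All of this stands and limits the harm. It does not remove the defect, because a stated rule that can divide by zero is more than a missing detail, and with no replication base rate fixed the condition for using it can readily be met.

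Four stronger readings are tempting but unsupported:
- **That the hypothesis "Base-rates will outperform the typical forecaster" is confirmed by construction.** It is framed in Brier scores and does not mention the fallback. The identity in Step 3 covers only constant forecasts; participants give a separate probability per study, and such forecasts can beat the variance.
- **That a knowledgeable forecaster is judged at .25 against .167 (p = .5, divisor N).** That average includes the undefined cases: .75 × .222 = .167. Where the score exists, the reference is .222.
- **That the two surveys always have different references.** Step 5 shows otherwise for three outcomes per question.
- **That skill scores were in fact undefined here.** Footnote 4 says neither that the fallback was used nor that either survey's outcomes were unanimous.

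**Conclusion.** The point holds as a defect in a secondary metric, of minor to moderate severity. Where the fallback is used, the individual skill score is undefined with probability 25%, 37% or 52% per question (three outcomes, assumed rates .5, .3, .2), or about 3%, 12% or 26% with six. Where it is defined, its zero point is set by the scored outcomes and an unstated divisor.

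These probabilities assume independent outcomes at a common rate. The two questions on one study are unlikely to be independent, so the six-outcome figures are only a guide. That three outcomes per question are scored is inferred from the survey design, not stated with the fallback.

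The damage falls on the website display, pooled ranks and tiers, and the predictor tests, which the protocol calls exploratory. A reader might infer that the main accuracy results are compromised. They are not: the primary endpoints and their power calculation use raw Brier scores against constants.

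**What to change.** Delete the sample-variance sentence and replace it with a rule such as: *If no external base-rate forecast was fixed before any outcome was known, BS_ref = .25 (a 50% forecast for every event) for all forecasters and both surveys. If one was fixed in advance, BS_ref is the Brier score of that forecast on the same events.*

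The second clause is needed because the present definition equates BS_ref with a rate, whereas the formula needs a score. Any base rate other than 50% has a realised score that varies with the outcomes. That is acceptable when the forecast itself was set beforehand, but skill scores from the two surveys should then not be pooled without allowing for survey version. Footnote 4 refers to observed results, so a base rate chosen after that point would not qualify.

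The cost is two sentences. The downside is that with .25 the skill score is only a rescaled Brier score, 1 − BS/.25 = 1 − 4BS, and adds no information. It does always exist, needs no divisor, and keeps zero at the value the protocol already treats as uninformed.

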| PRIMARY OBJECTIVES  To determine how well the expert cancer research community, in the aggregate, can forecast the overall replication rate of high impact preclinical cancer studies and the reproducibility of specific high impact basic and preclinical cancer experiments.  To determine how well individual experts in this community can forecast the overall replication rate of high impact preclinical cancer studies and the reproducibility of specific high impact basic and preclinical cancer experiments. |
| SECONDARY OBJECTIVES   1. What are the cognitive characteristics of the experts who update more appropriately? 2. Determine whether beliefs about the pace of progress in medical research (AKA medical boomster / doomster scale score) correlates with forecast skill. 3. Determine demographic characteristics of better forecasters. 4. Determine target study features (in vivo vs. in vitro, etc) with higher forecast success rates 5. How well do forecasters update after seeing results? 6. What are the demographic characteristics of experts who update more appropriately? 7. What types of evidence do the most effective forecasters prioritize, and what study features are easiest to predict? 8. Combine several above results to identify which trial and forecaster characteristics lead to more accurate forecasts. 9. Determine whether researchers who originate a report are more or less accurate than independent experts, individuals associated with the team replicating the experiment and non-experts. |
| METHOD OVERVIEW  We will use both ‘binary’ forecast methodologies (i.e. subjective probability on binary outcomes) to collect forecasts for individual replication studies, and ‘simplified continuous’ elicitations on select studies. When replication studies close, we will collect study outcomes, determine forecast scores using a proper scoring rule (called Brier score), and collect updated forecasts. |

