| SAMPLING  Study sampling and sample sizes:  Our study sampling frame will consist of all (approximately 35) studies being tested in the Reproducibility Project:Cancer Biology. We will categorize the studies based on theoretical and practical features. We will remove studies due to lack of feasibility (e.g. if there is not a clear relevant effect to predict, such as many in vitro studies especially those focused on cell signaling; if maturation date is too far in the future). We will prioritize studies whose results will be published sooner.  We will work with an independent expert to create or edit two to three questions for each study that can be rendered into dichotomized forecasts. In stage 1, participants will forecast all of the first six (all based on mouse models) studies from the cancer reproducibility project plans to publish. Participants will answer two binary elicitations for six events and simplified continuous elicitations for two events.  When mouse survival or tumor growth curves are used, questions will be created around them. When there are no mouse studies, we will shape a question around a study with a quantitative outcome. We plan to conduct a brief pilot to ensure the question types are relatively intuitive. Question formats might vary slightly depending on pilot results.  For the binary elicitation, our questions will take the two^[[2]](#footnote-2)^ of the following general forms:   1. How likely is it that the replication also be significant (at p ≤ .05)? 2. How likely is it that the effect size of the replication will be as large or larger than the original effect size?   For the simplified continuous elicitation (SCE) for the effect size of the specified treatment group, we will use a four question format, based on [9]:  1. What is the lowest effect size you realistically anticipate will be reported for study X?  2. What is the highest effect size you realistically anticipate will be reported for study X?  3. What is your best guess of the effect size you realistically anticipate will be reported for study X?  4. How confident are you (from 0% to 100%) that your estimated interval (lowest to highest) will include the reported effect size from study X?  Investigator sampling and planned strata:  All respondents will be at least 18 years old and will complete an informed consent.  Our primary sample will include two strata:  *a) Independent Experts*: we will create a sample of about 50 to 100 eligible independent international experts by compiling a list of authors from two searchers based on each original study undergoing replication: a) *related article* searches on PubMed and b) articles citing the original report. We will include corresponding authors and anyone who appears at least three times in any single search.  b) Novices: we will recruit a sample of about 50 to 100 medical undergraduate or upper level undergraduate biology majors, graduate students, or postdoctoral fellows at various universities via department mailing lists to participate in our study.  We will aim to include two secondary strata^[[3]](#footnote-3)^:  *c) Originators*: we will contact each co-author on each original research publication for an elicitation.  *d) Replicators*: we will contact each co-author on each replication protocol - only in cases where data collection has not yet been initiated.  Subjects will be approached through email (except non-experts, who may be approached in a class), and administered the questionnaire electronically.  Individuals will be approached up to five times before declaring them as having declined participation.  Sample size:  Our target sample size is as follows:  We will collect forecasts on 3 events in a half hour. We will collect 2 binary forecasts on 6 effects from 6 experiments + simplified continuous forecasts on overall replication rates). We will split the trial sample into two surveys to minimize the number of trials for which participants only have general expertise.  We will target 30 forecasts per participant on 6 events.  We will aim for 150 participants (50X2=100 independent experts + 50 novices) and expect a minimum of 90 (30X2=60 independent experts + 30 novices). |

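### The n = 34, and any 95% CI built on forecasters alone, hold only for the six named replications and cannot support a claim about the field

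*Protocol*

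**What the plan says.** **Power and comparison.** The Primary Analysis section sizes one group of forecasters against a fixed value: "An a priori power analysis suggests we need a sample size of 34 to detect if expert Brier scores are different than a constant". The constant is, for example, "random guessing (BS = .25"; the assumptions are "d = .5) assuming power = .80 and alpha = .05". The null is framed through "mean Brier score 95% confidence intervals exclude Brier score for a matched sample size of hypothetical forecasters predicting same trials using a random number generator".

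**Events.** The Interview and Data Collection section has each participant forecast "Significant difference and direction on 3 replication studies". The Sampling section speaks of "all of the first six (all based on mouse models) studies" but splits them into two surveys. Survey Versions fixes the sets: one survey has "Studies 15, 21, & 44", the other has studies 19, 29 and 39. So there are three shared outcomes per survey and six in the whole study, against a target of 100 experts and an expected minimum of 60.

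**Aim.** The first primary objective begins "To determine how well the expert cancer research community, in the aggregate, can forecast" and then names two targets: the overall replication rate of high impact preclinical cancer studies, and the reproducibility of specific experiments. The Introduction goes further and expects the results to show whether scientists, and their community, judge biomedical evidence shrewdly.

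**The concern.** A Brier score depends on the forecast and on the outcome. Within a survey the outcomes are common to everybody, so one study replicating or failing moves every score together. A standard error taken from the spread between forecasters cannot see that component. More forecasters make the interval narrower while the number of events stays at six. The six are also not a sample of the field: they are the first due to be published, and all use mouse models. If the interval is read as evidence on expert forecasting in general, a finding on either side of .25 may largely reflect which of six studies happened to replicate, reported with the precision of 60 to 100 people.

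**Working it through.** **Step 1. The plan's own figure.** Inputs from the Primary Analysis section: d = .5, power .80, alpha .05. A two-sided one-sample t-test (noncentral t) gives n = 34 with power .808; n = 33 falls just short of .80. The figure reproduces. The formula has one variance term, between forecasters, and none for studies.

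**Step 2. Outcomes held fixed.** In simulation at n = 34, the nominal 95% CI covers the conditional mean Brier score in 95.1% of runs with three fixed outcomes and 94.8% with six. As a statement about these outcomes the interval is sound.

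**Step 3. What one outcome does.** Let the mean forecast be m and the forecast variance s². The expected score is (1 − m)² + s² if a study replicates and m² + s² if it does not, a difference of 2m − 1. Over six equally weighted studies, one reversed outcome moves the mean by (2m − 1)/6. At m = .70 that is .40/6 = .067; within a single three-study survey it is .40/3 = .13. With s = .20, the mean score if k of six replicate is [.09k + .49(6 − k)]/6 + .04:
- k = 0: .53
- k = 3: .33
- k = 6: .13

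For scale, the simulated SD of scores across forecasters is about .12 to .14, so d = .5 corresponds to a Brier difference of about .06 to .07. One reversed outcome is as large as the effect the study is powered for.

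**Step 4. What remains however many forecasters are recruited.** If study outcomes are independent with replication probability p, the SD of the mean score as n grows without limit is |1 − 2m| × √(p(1 − p)/K). At m = .70, p = .70, K = 6 this is .40 × √(.21/6) = .075. In the two-survey simulation at m = .70 the actual SD of the mean is .074 at n = 60 and .075 at n = 100, while the nominal standard error falls from .016 to .012.

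**Step 5. How often the interval misses.** Assumptions, none of them in the protocol: forecasts carry no discrimination, forecast SD is .20, outcomes are independent, and there is one question per study. p is set so that the expected Brier score over new outcomes is .25: p(1 − m)² + (1 − p)m² + .04 = .25, hence p = (m² − .21)/(2m − 1). With 60 experts over two surveys of three studies:

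| Mean forecast m | p | Nominal 95% CI misses .25 |
|---|---|---|
| .55 | .925 | about 11% |
| .60 | .75 | about 42% |
| .70 | .70 | about 70% |
| .75 | .705 | about 72% |

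Bounding forecasts to 0–1 (which shifts p slightly) or adding a within-forecaster correlation of .3 moves these rates by up to about three points. The rate rises with recruitment: with both features, at n = 34, 60 and 100 it is about 33%, 44% and 54% for m = .60, and 61%, 68% and 71% for m = .70.

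**Step 6. Would resampling studies repair it?** In the m = .70 scenario, a bootstrap over forecasters and studies, stratified by survey, covers the expected score in about 82% of runs overall. When all six studies replicate, its interval is only about .07 wide and coverage is 0%. Footnote 4 reports little variability in the observed replication results, so this weakness matters here.

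**The case against.** The strongest reply is that the stated comparison is already conditional. The hypothetical forecasters face the same trials, and .25 is the score of a 50% forecast whatever happens. The objective also names specific experiments, not only the field. This stands: the miss rates above concern the expected score over new outcomes, a null the Primary Analysis section does not state. But matching on trials does not remove the luck of the outcomes. A constant 50% forecast scores .25, and a uniform random number has expected score 1/3, whichever way each study falls. The comparator stays still while the experts' scores move.

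Three further points also stand. The protocol does not say how the CI's standard error is formed, so a forecaster-only CI is an inference; only the power statement visibly rests on forecasters alone, and an SAP not shown may say more. The n = 34 sentence sits under the replicability-rate measures, and overall rates are also elicited by separate simplified continuous questions, so its link to the study-level scores is partly inferred. Each participant answers two binary questions per study, which the simulation does not model; the two share an experiment and are not independent events. None of this creates more than six studies.

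A reader might infer that n = 34 is miscalculated or that the CI is invalid. Steps 1 and 2 show neither is so.

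**Conclusion.** The concern holds as a limit on scope. The n = 34 with 80% power, and a CI built on the same basis, answer how these experts scored on six realized outcomes. They do not support the general aims in the Introduction and Primary Objectives. If used for those aims, the nominal 5% error becomes roughly 11% to 72% at n = 60 for mean forecasts of .55 to .75, under assumed forecast SD, replication probability, independence and absence of discrimination. A reader might take a figure near 70% as the study's false-positive rate. The documents do not support that: it belongs to one assumed mean forecast, lies near the top of the range, and refers to a null the protocol does not state.

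**What to change.** 1. In the Primary Analysis section, state that the 95% CI of the mean Brier score and the n = 34 with 80% power are conditional on the six named studies, and word the primary conclusion for those six.
2. Alongside the planned study-level Brier scores, show the mean Brier score with each single outcome reversed and with each study left out. Expect about .067 per reversed outcome over six at a mean forecast of .70.
3. Make no field-level claim with a forecaster-only interval. Do not rely on a forecaster-by-study bootstrap to support one: with six outcomes that vary little it can be falsely narrow.

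The cost is a narrower conclusion and a little extra analysis. No new data are needed.
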